### Interim analyses {21b}

No interim analysis is planned.

### Methods for additional analyses (e.g. subgroup analyses) {20b}

Additional analysis in the ITT population and the per-protocol (PP) population will include important sub-groups such as infants exposed to HIV infection and those delivered by Caesarean section. Additional analyses may be considered should any new information become available.

### Methods in analysis to handle protocol non-adherence and any statistical methods to handle missing data {20c}

Analyses of the PP population will be a sensitivity analysis to investigate whether conclusions are sensitive to assumptions regarding compliance with the dietary supplements and missing data. Maximum efforts will be made to avoid missing values; however, where this does occur, missing data will be reported and left out of analyses.

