## Assignment of interventions: allocation

### Sequence generation {16a}

The trial statistician at LSTM, UK, will prepare computer-generated random allocation sequences using blocks of random size and stratified according to HIV exposure. The allocation ratio will be 1:1:1:1.

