## Statistical methods

### Statistical methods for primary and secondary outcomes {20a}

Demographic, clinical and laboratory data and also variables reflecting feeding, WASH practices and environmental factors will be summarised using simple descriptive statistics. Continuous variables will be summarised according to the number of subjects with non-missing data as mean, standard deviation, median, minimum and maximum. Categorical variables will be summarised according to the absolute frequency and percentage of subjects in each category level. The denominator for the percentages is the number of subjects with data available unless noted otherwise.

The primary outcome analysis will be based on the intention-to-treat (ITT) population which will include all randomised study subjects. The proportion of infants aged 6 months with abnormal AGP concentration (> 1 g/L) in each intervention arm will be compared with the proportion in the control arm. Data will be analysed using generalised linear models with treatment as the only predictor, AGP concentration at baseline as covariate, binomial distribution and log link function, generating the estimates of treatment effects in relative risk and their 95% confidence intervals (CI). Covariate-adjusted analysis will also be performed with covariates that affect the primary outcome (e.g. season of birth, HIV exposure, mode of delivery, mode of feeding, exposure to antibiotics, WASH and environmental factors such as water source, sanitation facilities, hygiene practices, use of soap, number of siblings, proximity to animals). Subgroup analysis will also be performed on the covariates used in the covariate-adjusted analysis.

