Analysis of the secondary endpoints with single measurements will also be presented in the ITT and per-protocol (PP) populations and in a similar fashion as for the primary endpoint analysis using generalised linear method. The PP population will be all randomised study subjects who complete 75% or more of the supervised doses. For continuous outcomes, normal distribution and identity link function will be used, from which mean difference together with its 95%CI will be derived. Generalised linear mixed model (GLMMIX) will be employed for the analysis of secondary outcomes with repeated measurements. The GLMMIX model will have treatment, visit, interaction between treatment and visit as fixed effects, baseline measurement of an outcome as covariate, and subject as random effect. The treatment difference between two treatment arms at each visit together with its 95% confidence interval will be derived from the GLMMIX model. Missing data will be treated as missing completely at random in the GLMMIX model analysis and no imputation of primary or secondary endpoints will be made. For the analysis of binary secondary outcomes with repeated measurements, the GLMMIX model will have a binomial distribution and logit link function. The odds ratio between two treatment arms at each visit together with its 95% confidence interval will be derived from the GLMMIX model. For the analysis of continuous secondary outcomes with repeated measurements, the GLMMIX model will have a normal distribution and identify link function. The mean difference between two treatment arms at each visit together with its 95% confidence interval will be derived from the GLMMIX model.

For anthropometric outcomes, *z* scores will be calculated using the WHO Anthro Survey Analyser and WHO 2006 child growth standards [47]. Analyses will include both the comparison of anthropometric indices between intervention groups at different time points and also growth expressed as change in indices over time.

Analyses of the potential adverse effects of the dietary supplements will be done in the safety population.

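### The unrestricted rule to leave missing data out of analyses makes the additional covariate-adjusted analysis drop infants whose 6-month AGP was measured

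*Protocol article*

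**What the plan says.** Three statements in the protocol article bear on this.

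- **General rule, section {20c}.** On missing values: "where this does occur, missing data will be reported and left out of analyses". No type of variable is exempted.
- **No-imputation statement, section {20a}.** Here the limit is explicit: "no imputation of primary or secondary endpoints will be made". Covariates are not mentioned.
- **Analyses of the primary outcome, section {20a}.** The main analysis uses "generalised linear models with treatment as the only predictor, AGP concentration at baseline as covariate, binomial distribution and log link function", in the "intention-to-treat (ITT) population which will include all randomised study subjects". A further analysis is then promised: "Covariate-adjusted analysis will also be performed with covariates that affect the primary outcome (e.g. season of birth, HIV exposure, mode of delivery, mode of feeding", continuing with "exposure to antibiotics, WASH and environmental factors such as water source, sanitation facilities, hygiene practices, use of soap, number of siblings, proximity to animals". The list is introduced as examples, so the final set is open.

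No section says what happens to an infant whose 6-month AGP is known but who has a blank covariate. None provides a missing category or imputation for covariates.

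**The concern.** A multivariable model that leaves out missing data keeps only infants who are complete on every variable in it. The infants lost this way are not lost to follow-up: their outcome was measured, and only a background item such as water source or number of siblings is blank. In a randomised comparison, a blank in a variable describing status at enrolment is no reason to discard the infant.

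Two things are at stake. The adjusted analysis gives up outcome data that were collected. And the adjusted and unadjusted relative risks could differ merely because they rest on different infants, which makes their comparison hard to read. It also moves the adjusted analysis further from a population of all randomised infants.

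**Working it through.** **1. Reproduce the planned number.** Inputs from Sample size {14}: 35% against 17.5%, α = 0.0167, 80% power. The article does not state sidedness; two-sided reproduces its figure. With pooled variance and no continuity correction,

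n = [z(1−α/2)·√(2p̄(1−p̄)) + z(0.80)·√(p₁(1−p₁)+p₂(1−p₂))]² / (p₁−p₂)²

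with p̄ = 0.2625, z(1−α/2) ≈ 2.393 and z(0.80) ≈ 0.842:

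n = [2.393×0.6222 + 0.842×0.6098]² / 0.175² ≈ 131 per arm.

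This matches the stated 131 (524 in all). Power at 131 is 80.0%.

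**2. Count the covariates that can be blank.** The eleven named examples are season of birth, HIV exposure, mode of delivery, mode of feeding, antibiotics, water source, sanitation, hygiene, soap, siblings and animals. HIV exposure must be known before allocation, because Sequence generation {16a} describes "computer-generated random allocation sequences using blocks of random size and stratified according to HIV exposure". Season follows from the birth date, which the age criterion already needs. That leaves at most about 9. Participant timeline {13} ties the feeding, WASH and environmental items to questionnaires, and Data management {19} says these are on paper.

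**3. Share kept under the rule.** The article gives no missingness rate, so the per-item rate m is an assumption. If k items are blank independently, the share kept is (1−m)^k. For k = 9 and m = 1%: 0.99⁹ = 0.9135, and 131 × 0.9135 = 119.7 per arm. The standard error grows by 1/√0.9135 = 1.046. Power is the two-proportion power at the reduced n, used as an unadjusted approximation.

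| Blank per item (assumed) | Share kept, 9 items | Infants per arm | Increase in SE | Power |
|---|---|---|---|---|
| 0% | 1.000 | 131 | 0% | 80.0% |
| 0.5% | 0.956 | 125.2 | 2% | 77.9% |
| 1% | 0.914 | 119.7 | 5% | 75.7% |
| 2% | 0.834 | 109.2 | 10% | 71.1% |
| 5% | 0.630 | 82.6 | 26% | 56.6% |

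**4. Vary the number of items.** With 8 items, 1% and 5% give 120.9 and 86.9 per arm (power 76.2% and 59.2%). With all 11 named examples they give 117.3 and 74.5 (74.7% and 51.4%), but that count includes the two variables that should always be known.

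**5. Vary the independence assumption.** If the blanks all fall in the same infants, the share lost is just m. Then 0.5%, 1%, 2% and 5% leave 130.3, 129.7, 128.4 and 124.4 per arm. Real data would lie between this and step 3.

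**The case against.** The strongest reply is that handling of blank covariates in a supplementary analysis belongs in the analysis plan. The article condenses a longer protocol, and Who will be blinded {17a} confirms that a plan will be signed off before allocation is released. That would answer silence, but the article is not silent. It states a rule without restriction, and a plan that kept these infants would depart from its wording.

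It is also fair to say that the rule never names covariates. Applying it to them is the plain reading of an unrestricted sentence, not an express provision. The contrast with the no-imputation statement, which is limited to endpoints, supports that reading but does not prove intent.

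The size is uncertain and may be small. Staff administer the questionnaires, section {19} provides missing-data checks and source verification, and weekly visits to 6 months give chances to recover household facts. Items collected together tend to be blank together. The 80% power target belongs to the sample-size comparison; none is claimed for the adjusted analysis. All of this stands.

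Three stronger readings are tempting, and the article supports none of them:

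- **The main primary analysis loses these infants.** It does not; its model holds only treatment and baseline AGP. Blood sampling is first scheduled at 6 weeks, so whether a baseline AGP exists at all is a separate question, which this point does not rely on.
- **Any one of eleven questionnaire items can remove an infant.** The list is open, and two of the eleven should always be known.
- **The adjusted estimate will be biased.** Nothing here shows that. Blanks unrelated to arm and outcome cost precision only.

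**Conclusion.** The point holds for the additional covariate-adjusted analysis of the primary outcome. Taken as written, section {20c} makes that analysis complete-case and discards infants with a measured 6-month AGP.

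Under assumed independent blanks of 0.5% to 5% in each of 9 items, the loss runs from about 4% to 37% of evaluable infants. If blanks cluster fully, it is only about 0.5% to 5%. The result rests on three assumptions: that the rule extends to covariates, that most of the example covariates enter the model, and the missingness rates, which the article does not give. The harm is avoidable imprecision and a mismatch between the infants behind the adjusted and unadjusted results. The wording deserves correction because the remedy is nearly free; the main analysis is not threatened by blanks in these items.

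**What to change.** In section {20c}, limit the instruction to leave missing data out so that it applies to outcomes only, and add:

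*In adjusted analyses every randomised infant with an observed outcome is kept. A missing covariate describing status at enrolment is filled without reference to arm (a separate missing category for categorical items, the overall mean for continuous items), and the number filled is reported by arm.*

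The wording refers to status at enrolment, not to the time of recording, because section {13} describes the questionnaires after allocation. Variables that can change after randomisation, such as later feeding mode or antibiotic exposure, fall outside this rule; only their enrolment values should be used in the adjusted model. Nor is the rule a remedy for a baseline AGP that was never sampled.

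The cost is two sentences and a few lines of code, with no new data. The downside is slightly weaker adjustment for the filled values.

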#### Secondary outcomes

Biomarkers at ages 6 weeks and 3, 6 and 12 months
Plasma marker of chronic inflammation: (AGP; at 6 weeks and 3 and 12 months)Stool biomarker of intestinal inflammation: myeloperoxidaseStool biomarker of intestinal permeability: α1-antitrypsin (AAT)Plasma marker of acute inflammation: C-reactive protein (CRP)Plasma marker of gut mucosal integrity: intestinal fatty acid-binding protein (IFABP)Plasma growth hormones: insulin-like growth factor (IGF)-1 and its carrier protein IGF-binding protein 3Stool pH

Clinical outcomes to age 2 years
MortalityHospital admissionAll-cause sick-child clinic visitsDisease-specific sick-child clinic visits (e.g. diarrhoea; respiratory and skin infections)Anthropometric outcomes: weight, length, mid-upper arm circumference (MUAC), head circumference

Feeding and WASH practices and environmental factors that may influence the development of the gut microbiome will be assessed by questionnaires.

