### Sample size {14}

A total of 600 newborns will be recruited. For the primary outcome, we predict raised AGP (> 1 g/L) in 35% infants at age 6 months in the control group [22]. The study requires a total of 524 infants (131 per am) to demonstrate a 50% reduction (relative risk = 0.50) in the prevalence of the primary outcome from 35% in the control arm to 17.5% in any of the intervention’s arms with 80% power and *α* = 0.0167. The alpha of 0.0167 is required to allow for three comparisons, one for each intervention arm, against the control arm. We will recruit 150 infants per group to allow for 13% dropouts.

We have used AGP concentration as a dichotomous outcome as a conservative approach as we wish to recruit sufficient numbers of children to compare other important biomarkers between groups. Using values of biomarkers as continuous variables will increase the power of the study to detect differences between the study arms. Using AGP as an example, we predict a mean log_10_ value of − 0.24 g/L in controls based on data from Zimbabwe [20]. In total, 102 infants in the intervention and the control group are required to show that mean AGP concentration is 20% lower in the intervention compared with the control group with 90% power at the 5% significance level.

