Laboratory assays will be carried out according to the manufacturer’s instructions. All assays will be carried out in duplicate and repeated should there be a discrepancy in values. Processing, analysis and storage of samples will be undertaken at the Research Laboratories at the Kenya Medical Research Institute (KEMRI) Centre for Global Health Research, Kisumu, Kenya.

Clinical outcomes will be assessed as follows:
Mortality and hospital admissions will be recorded by a questionnaire applied during each scheduled and unscheduled visit and information copied from any health cards carried by the mother/carer and/or from hospital records and reported as serious adverse events (SAEs).Episodes of all-cause and disease-specific sick-child clinic visits will be recorded during each scheduled visit as reported by the mother/carer and information copied from any health cards carried by the mother/carer and/or from clinic records.Weight will be measured to the nearest 100 g using electronic scales. MUAC will be measured at the mid-point between the tip of the shoulder and the tip of the elbow using a non-stretchable MUAC tape to the nearest 0.1 cm. Length will be measured to the nearest 0.1 cm using a length board. Head circumference will be measured to the nearest 0.1 cm using a non-stretchable tape measure. All measurements will be performed in duplicate and a third measurement made should values disagree by a pre-specified amount. Scales and length boards will be checked daily for accuracy using a standard weight and a ruler.

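### Sick-child clinic visits and admissions recur over two years, but the plan names only binomial and normal models and no time at risk, so partly followed infants are handled inefficiently and, for totals, ambiguously

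*Protocol article*

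**What the plan says.** The Secondary outcomes section lists mortality, hospital admission, and all-cause and disease-specific sick-child clinic visits under "Clinical outcomes to age 2 years". Section {18a} describes how they are captured: "Episodes of all-cause and disease-specific sick-child clinic visits will be recorded during each scheduled visit", and "Mortality and hospital admissions will be recorded by a questionnaire applied during each scheduled and unscheduled visit". The adverse-event section {22} adds that illness is also followed to age 2 by monitoring attendances at the research facilities.

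Section {20a} sets the models. Secondary endpoints measured once are handled like the primary (binomial, log link), and "For continuous outcomes, normal distribution and identity link function will be used". For repeated measurements there is a mixed model with treatment, visit and their interaction as fixed effects and subject as a random effect. For binary outcomes "the GLMMIX model will have a binomial distribution and logit link function"; for continuous ones "the GLMMIX model will have a normal distribution and identify link function". Missing values are assumed missing completely at random and are not imputed. Section {20c} adds that "missing data will be reported and left out of analyses".

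The only allowance for loss is in Sample size {14}: "We will recruit 150 infants per group to allow for 13% dropouts". It belongs to the 6-month primary outcome. No two-year figure is given.

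**The concern.** An infant can have several clinic visits or admissions, and the number depends on how long the infant is watched. The models named are for a yes/no result or a normally distributed value. None has an exposure term, and no rule says how an infant who dies, withdraws or moves away counts towards a two-year total.

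Three routes remain within the stated methods:

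- **Total among completers.** The total of an infant who leaves is incomplete, hence missing, hence left out along with the events already seen.
- **Total taken as it stands.** Short follow-up looks like good health, and so does an early death.
- **Outcome by visit interval in the mixed model.** Completed intervals are kept, but repeat episodes become yes/no or are fitted as normal.

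Reducing episodes of illness is one of the trial's secondary objectives. What is at stake is the precision of that comparison and, under the second route with unequal loss, its direction.

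**Working it through.** **The plan's own figure.** The article gives no sample size or event rate for visits or admissions; its only design figure is for the primary outcome. With 35% vs 17.5%, two-sided alpha 0.0167 and 80% power (pooled variance), n = [2.393·√(2·0.2625·0.7375) + 0.842·√(0.35·0.65 + 0.175·0.825)]² / 0.175² = 131 per arm, 524 in total, as stated. Then 131/0.87 = 150.6, close to the stated 150. The present point does not touch this calculation.

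**Assumptions.** These are not in the article: a constant event rate, exits uniform over T = 2 years, and loss d of 5% to 30%, with 13% borrowed from the 6-month allowance.

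**Route 1, leavers excluded.** A leaver is observed for T/2 on average, so the share of observed events discarded is (d/2)/(1 − d/2). At d = 0.13 this is 0.065/0.935 = 7.0%. At 5%, 20% and 30% it is 2.6%, 11.1% and 17.6%.

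**Route 2, partial totals read as complete.** The mean count is understated by d/2: 6.5% at d = 0.13, and 2.5%, 10% and 15% at 5%, 20% and 30%. With no true effect and losses a and b, the ratio of mean counts is (1 − b/2)/(1 − a/2):

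- 13% vs 13%: 1.00
- 9% vs 17%: 0.915/0.955 = 0.96
- 8% vs 18%: 0.91/0.96 = 0.95
- 10% vs 25%: 0.875/0.95 = 0.92

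Bias appears only when loss is unequal.

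**Route 3, by visit interval.** Data-collection visits at 6 weeks and 3, 6, 12 and 24 months give intervals of about 1.4, 1.6, 3, 6 and 12 months. If only the interval of exit is dropped, a leaver loses on average Σ(L²/2)/24 = (1.96 + 2.56 + 9 + 36 + 144)/48 = 4.0 months of observed time. Total observed time averages 24 × 0.935 = 22.4 months per infant, so the loss is 0.13 × 4.0/22.4 = 2.3% of events, and 97–98% are kept. The longest interval, 12 to 24 months, is half of follow-up and accounts for most of this loss.

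**Any/none.** With a negative binomial count of mean m and dispersion 0.5, P(at least one) = 1 − (1 + 0.5m)⁻². At 3 visits per year over two years, m = 6 in controls gives 1 − 1/16 = 94%. With a rate ratio of 0.75, m = 4.5 gives 1 − 1/3.25² = 91%. A 25% reduction in episodes shows as a difference of about 3 points.

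**Power.** Simulation with 150 per arm, dispersion 0.5, rate ratio 0.75, 13% leaving in each arm and alpha 0.0167 (the article's primary-outcome level, borrowed); 1,500 replicates:

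| Visits per year | Any/none, completers | Normal, completers | Negative binomial, person-time offset |
|---|---|---|---|
| 1 | 13% | 42% | 47% |
| 3 | 6% | 65% | 71% |
| 5 | 2% | 68% | 75% |

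The gain over the normal model is 5, 6 and 7 points. The Monte Carlo standard error is about 1.2 points (√(0.7·0.3/1500)), and a repeat with 6,000 replicates agreed to within two points. The rate model was given the true dispersion, which flatters it slightly.

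**False positives with no effect, 3 visits per year, nominal 1.67%.** Partial totals read as complete give 4.5% to 7% across runs at 10% vs 25% loss, but only 2% to 3% at 9% vs 17%. The completers-only normal analysis stays at about 1.7% even at 10% vs 25%. The offset model has a mean rate ratio of 1.00.

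**If admission is read as ever/never.** At an assumed 0.3 per child-year, the true two-year risk is 1 − e^(−0.6) = 45.1%. With 13% leaving, 24.8% of leavers have an event before exit. Scoring the other leavers as no gives 0.87·0.451 + 0.13·0.248 = 42.5%. Excluding them but keeping leavers with an event gives 0.425/(0.87 + 0.032) = 47.1%.

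**The case against.** The strongest reply has four parts.

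*This is analysis-plan detail.* Section {17a} refers to a separate statistical analysis plan, and the article never calls visit counts continuous or binary; the outcome list even has admission in the singular. In part this stands: the analysis plan may already name a count model. But the article does more than stay silent. It states the model families for secondary outcomes and a leave-out rule, and these do not suit recurrent events under unequal follow-up.

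*Infants who leave can be scored.* A reader might infer that they cannot be analysed at all, or that their events are necessarily lost or miscounted. The documents do not support that. Episodes are recorded visit by visit, the mixed model uses the visits attended, and leaving out missing data need not mean dropping the infant. By interval, 97–98% of observed events survive under the assumptions above. What remains is the poor fit of yes/no or normal models to repeat episodes, the dropped interval of exit, and no stated overall rate ratio. The article also does not say that this route applies to these outcomes.

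*Bias is not shown.* This stands. Completers-only analysis is unbiased when leaving is non-informative, and no passage prescribes reading partial totals as complete. Loss could differ by arm, since the trial is open-label and section {11b} lets carers withdraw over concerns about harm from the supplement. But controls get the same home visits, supplementation ends at 6 months, and nothing predicts an imbalance.

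*The inputs are assumed.* Also right. The article gives no clinic-visit frequency, so it cannot be said that nearly every child will have one, and it does not state that dates of exit are recorded.

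**Conclusion.** The point holds in a limited form. The stated methods contain no count model and no time at risk for outcomes that accumulate to age 2 years, and the leave-out rule does not settle how partly observed infants enter a total. The cost is mainly efficiency: about 7% of observed events if leavers are excluded at 13% evenly spread loss (2.6% to 17.6% for 5% to 30%), about 5 to 7 points of power against the normal model at 1 to 5 visits per year, and a large loss if episodes are collapsed to any/none. Bias needs both unequal loss and partial totals read as complete; the count ratio is then about 0.92 to 0.96 in the examples tried.

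Event rate, dispersion, rate ratio and loss pattern are all assumptions. Only secondary outcomes of a trial that describes itself as exploratory are involved. The change is worth making because it is nearly free.

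**What to change.** State in the statistical analysis plan, before the allocation is released, that sick-child clinic visits (all-cause and disease-specific) and hospital admissions will be analysed with a negative binomial (or robust Poisson) model with log link, log person-time as offset, and adjustment for the HIV-exposure stratum. Every randomised infant contributes from enrolment to death, withdrawal or last contact. Report rate ratios with confidence intervals for 0–6 months and 0–24 months.

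The cost is a few sentences and some data work: dates of exit or last contact must be taken from visit and withdrawal records. The model assumes that leaving is non-informative given its terms, so loss and person-time should be tabulated by arm beside the results. No change to the primary analysis, the sample size or the visit schedule is needed.
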